### Participant incentives

3.5

Aim 1 was conducted on a volunteer basis by the research team and fire service expert panel with no formal compensation for the alpha and pre-beta testing of the development phase. For Aim 2 on usability (beta testing) among 50 enrolled new firefighters, we will conduct Focus Groups via Cambridge Health Alliance (CHA) Google Meet (expected n=25) compensated with a gift card, and satisfaction surveys (expected n=30) compensated by a gift card to get additional “end-user” feedback. For Aim 3, ~50 new firefighters will be recruited for pilot testing and their app usage will be monitored if they have completed more than three months of use (expected n=50). Upon completion of the pilot phase, participants will be given an additional gift card for a follow-up collection of health measures to compare against their baseline values.

### Statistical analysis

3.6

All data will be collected using de-identified study codes. Initial data merging, cleaning, management and basic statistical analyses will be performed using appropriate statistical software such as R software (version 4.1.0) (58) and Stata version 17.0 (59). For Aim 2, mixed methods will be applied, in which quantitative data will be collected through a satisfaction survey and qualitative data via focus group interviews. The latter will be analyzed using the thematic analysis method (60). After the focus group transcripts have been coded, they will be re-read to ensure that all relevant extracts have been identified and coded against the most appropriate theme. The themes will be grouped into main themes and subthemes, which will be hierarchically organized to reflect their prevalence in the data.

Regarding quantitative data (i.e., satisfaction survey data from the beta testing and all data collected from the pilot phase), continuous characteristics that are normally distributed will be presented as the mean ± SD and comparison between pre- and post- app usage using the paired t-test (or the repeated measures analysis of variance (ANOVA) for more than two groups), whereas those with skewed distributions will be presented as the median and interquartile range, and compared using non-parametric techniques such as the paired Wilcoxon test for two groups or the Friedman test for more than two groups. Dichotomized or categorical characteristics will be described as a frequency (%) and pre- and post- values compared using McNemar’s test or the chi-square test of independence, as appropriate.

In the pilot study phase, Aim 3, adherence to the HLS app will be measured continuously as the total number of engagements with the software by each participant over the 3 to 6-month pilot study. This outcome will be supported by other prespecified app-usage metrics facilitated by the Managed IT Services provider (i.e. app user information; sign-ins, quest completion rate for each level, frequency of habit tracker use, and number of missions initiated). The primary outcome for validating the efficacy of the HLS app among the new firefighters’ will be the changes in the HLS score, comparing the participants’ pre- and post- app-usage scores (10). Using a behavior change measure (i.e. HLS score) as a primary outcome is justified in an intervention of short duration (11). As secondary outcomes, we will evaluate changes in 1-min pushups and mental health parameters. In addition, we will examine whether the health culture in various fire service workplace environments, as measured by the Health Culture score, influences the intervention effect of the app on the primary and secondary outcomes.

Generalized linear models will be utilized to assess the effect of the proposed app intervention comparing pre and post HLS scores, mental health scores, and 1-min push-up capacity upon completion of 3-6 months of app usage. All models will have their assumptions verified, using analysis of the residuals and other diagnostic testing. Generalized linear modeling will be used to model changes over time after taking into consideration the specific variance-covariance structure of repeated measurements or using other statistical methods such as generalized estimating equations models. All models will be adjusted for demographic and working conditions and other potential confounders. Interaction terms will also be incorporated into the models to evaluate any potential effect modification by working conditions, cultures, and policies. Statistical significance for all analyses will be considered as a two-tailed *p*<0.05.

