## Abstract

In the United States (US), new firefighters’ fitness and health behaviors deteriorate rapidly after fire academy graduation. Over the long-term, this increases their risks for chronic diseases. This study protocol describes the proposed usability testing and pilot study of a newly designed and developed healthy lifestyle smartphone app, “Surviving & Thriving”, tailored towards young US firefighters. “Surviving & Thriving” will provide interactive educational content on four lifestyle factors; nutrition, sleep, physical activity, and resilience, and include a personalized journey, habit tracker, and elements of gamification to promote engagement and long-term healthy behavior change. The first phase of the app development entails alpha testing by the research team and pre-beta testing by a fire service expert panel which will help refine the app into a pre-consumer version. Upon completion of the full app prototype, beta ‘usability’ testing will be conducted among new fire academy graduates from two New England fire academies to collect qualitative and quantitative feedback via focus groups and satisfaction surveys, respectively. A last phase of piloting the app will evaluate the app’s efficacy at maintaining/improving healthy lifestyle behaviors, mental health metrics, and physical fitness metrics. We will also evaluate whether firefighters’ perceived “health cultures” scores (ratings of each fire station’s/fire department’s environments as to encouraging/discouraging healthy behaviors) modify the changes in health metrics after utilizing the app for three to six months. This novel user-friendly app seeks to help new firefighters maintain/improve their health and fitness more effectively, reducing their risk of lifestyle-related chronic disease. Firefighters who can establish healthy habits early in their careers are more likely to sustain them throughout their lives.

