Career firefighter recruits in the US typically undergo formal training in a designated Fire Academy for 12-20 weeks before becoming new or “probationary” firefighters during their first year of service (26). A recent study demonstrated that fire academy training significantly improved recruits’ body composition, aerobic capacity (1.5-mile run), muscular strength (push-up and pull-up), and muscular endurance (10). However, these fitness and health benefits significantly decreased before these recruits finished their probationary period after academy training. Moreover, firefighters after graduating from the fire academy began to exercise less, eat more poorly, and blood pressure continued to increase despite the health/fitness improvements gained during academy training (7, 24, 27). Nonetheless, a recently implemented HLS intervention in firefighters’ academy training showed improvements in healthy lifestyle behaviors, blood pressure, and mental health (11).

The primary aim of this study is to develop and pilot a user-friendly HLS smartphone application (app) tailored towards new probationary firefighters to consolidate and extend academy/training-derived health benefits into firefighters’ first year in the fire service, and then beyond. The first phase of our research project includes the compiling and designing of educational content for a multicomponent lifestyle intervention addressing physical activity, nutrition, sleep, and resilience, the corresponding app software development, and testing of the minimal viable product (MVP). In the second and third phases of this project, we will test the final HLS app prototype’s user-acceptance and effectiveness. The pilot study will evaluate the app’s ability to engage new firefighters and demonstrate whether adherence to the HLS app-based content is associated with measurable health benefits. New firefighters who can maintain a healthy lifestyle during their initial year in the fire service will be more likely to maintain good health behaviors throughout their careers.

We propose the following three aims for the development, usability testing, and piloting of this novel study intervention tool:

Aim 1- HLS app prototype: Develop a smartphone app for future utilization as a digital HLS intervention directed at new US firefighters. Alpha testing by the study team and pre-beta testing by a fire service expert panel will provide feedback on the MVP to enhance the ‘end-user ready’ *Surviving & Thriving* app.

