### Pilot study phase

3.3

This phase of the study aims to demonstrate that enrolled participants from the new firefighter study population can maintain adherence to the HLS app for at least 3-6 months. We will recruit ~50 new firefighters (a separate cohort from those enrolled in the beta testing) and monitor their app usage. App metrics such as session duration, screen views, and user retention within the app will provide insights into how users interact with the app over time. This cohort of new firefighters for the pilot study phase will also assess the HLS app’s ability to maintain/improve HLS parameters (HLS scores, physical fitness, mental health (trauma/depression) screeners). For the purposes of this pilot study, we will conduct a small single arm trial which aims to obtain preliminary evidence of the efficacy of a novel digital intervention and to collect qualitative feedback from a subgroup of target users. Changes in HLS parameters throughout the pilot testing will be evaluated with repeated measures of health metrics pre-and-post app usage among those participants that engaged in the HLS app for 3-6 months. Namely, participants will receive the same lifestyle and mental health questionnaires and fitness test at the two time points: before using the HLS app and at the subsequent follow-up (i.e. 3-6 months after). Both adherence and efficacy results will be adjusted for the potential influence of new firefighters’ demographic characteristics. Effect modification analysis will include fire crew, station and department cultures/policies (measured by the “Health Culture” score as mentioned below in 3.3.4.).

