### Covariates

3.4

Socio-demographic characteristics (i.e., age, sex, educational level, marital status) as well as behavioral health information will be collected via the online survey. Working conditions & fire department culture/policies will be measured post- app usage by means of “health culture” scores (**Table 1**). These scores rate the extent to which a new firefighter perceives that his/her department and co-workers value and promote healthy behaviors. Because we are unaware of any such previously validated instrument, with the input and oversight from our fire service expert panel, we have modified a set of questions from the Fire service Organizational Culture of Safety (FOCUS) survey with the addition of some questions on health-promoting environments used in other occupational settings (56, 57).

**Table 1 T1:** Data Collection during the Pilot Study Phase of the *Surviving & Thriving* app.

Study Measures	Pre-app usage: <1 year from Fire Academy graduation	Post-app usage: 3-6 months of app engagement
Healthy Lifestyle questionnaire	**X**	**X**
Physical Fitness Measure (i.e., 1-min pushups)	**X**	**X**
Mental Health: Depression/Trauma symptoms (BDI-PC, PHQ-9 and PCL-5)	**X**	**X**
“Health Cultures” scores: ratings of each fire station’s/fire department’s environments (working conditions, culture/policies) as to encouraging/discouraging healthy behaviors)	–	**X**

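### In a single arm, the Health Culture interaction tests whether pre-post change varies with perceived culture; it cannot show that culture modifies the app's effect

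*Protocol article*

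**What the plan says.** Section 3.3 (Pilot study phase) fixes the design: "we will conduct a small single arm trial which aims to obtain preliminary evidence of the efficacy of a novel digital intervention". On size it says "We will recruit ~50 new firefighters". Questionnaires and the push-up test are taken twice, before app use and 3 to 6 months later. The same section announces an effect modification analysis covering crew, station and department culture, measured by the Health Culture score.

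Section 3.6 (Statistical analysis) treats the pre-post comparison as the effect of the app. It then asks whether health culture "influences the intervention effect of the app on the primary and secondary outcomes", and gives the method: "Interaction terms will also be incorporated into the models to evaluate any potential effect modification by working conditions, cultures, and policies". Significance is two-tailed p<0.05 for all analyses.

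Section 3.4 (Covariates) describes the modifier: "These scores rate the extent to which a new firefighter perceives that his/her department and co-workers value and promote healthy behaviors".

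The Introduction describes what happens to recruits after they leave the academy: "these fitness and health benefits significantly decreased before these recruits finished their probationary period after academy training".

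The Abstract puts the culture question differently. It asks whether culture scores "modify the changes in health metrics after utilizing the app for three to six months".

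**The concern.** The question in 3.6 is about the app: does it work better or worse depending on workplace culture? The analysis answers a different one: does change over the follow-up period differ by culture? The two coincide only if culture has no bearing on how lifestyle, fitness and mental health would have changed without the app.

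The protocol gives reason to doubt that. It expects deterioration after graduation, and it builds a score for how far the workplace encourages healthy behaviour. A supportive station could plausibly slow the deterioration whether or not its firefighters use the app. A positive interaction could then be written up as modification of the app's effect when that effect is the same everywhere.

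This is separate from the fact that Table 1 collects the score only after app use. Measuring culture at baseline would leave the problem in place.

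**Working it through.** The protocol gives no power or sample-size figure for this analysis, so there is none to reproduce. The check is an identification argument followed by an illustration.

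**Identification.** Let C be the standardised Health Culture score. Expected change from first to second visit is

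E[change | C] = (d + b·C) + (a + m·C)

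- d: average change that would have occurred without the app
- b: culture's own influence on that change
- a: average effect of the app
- m: modification of the app's effect by culture

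With two visits and one arm, the interaction of culture with pre/post equals the slope of change on C, which is **b + m**. Section 3.6 asks about m. Nothing in a single arm estimates b, so m cannot be recovered. Adjusting for working conditions does not help: a main effect of culture absorbs differences in level between participants, not differences in drift.

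**Illustration.** Inputs:

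- From the protocol: n=50 (3.3), two visits (3.3), two-sided 5% (3.6).
- Assumed: normally distributed outcome with SD 1 at each visit and within-person correlation r, so SD of change = √(2(1−r)). At r=0.5 this is √(2×0.5) = 1.
- Assumed: m=0, so the app's effect is identical at every culture level.
- Assumed: b from 0 to 0.3 SD per SD of culture. The protocol gives no value, and its Discussion says evidence on health-promoting climates in the fire service is limited.

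Rate at which the slope test rejects (20,000 simulated trials per setting):

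| b | r=0.5 (SD of change 1) | r=0.7 (SD of change √0.6 ≈ 0.77) |
|---|---|---|
| 0 | 4.9% | 4.8% |
| 0.1 | 10.7% | 14.2% |
| 0.2 | 27.8% | 42.0% |
| 0.3 | 53.5% | 74.5% |

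A second, independently coded simulation with SD of change 1 gave 5.2%, 27.7% and 53.2% at b=0, 0.2 and 0.3. As a rough hand check at b=0.3, the expected test statistic is about 0.3×√49 = 2.1 against a critical value of 2.01 on 48 degrees of freedom, so rejection a little over half the time is what one expects. With 30 participants, r=0.5 and b=0.3, the rate is 34.7%.

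**What removes the problem.** In a hypothetical two-arm design with 50 per arm, SD of change 1 and m=0, the culture-by-arm test of change rejects 4.9%, 5.0%, 5.1%, 5.1% and 5.1% of the time at b = 0, 0.2, 0.3, 0.4 and 0.5. The concurrent control cancels b. The cause is therefore the missing comparator, not the choice of model.

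**The case against.** **It follows from a declared single-arm pilot.** The average pre-post change is confounded with background decline in the same way, and the protocol claims only preliminary evidence, with a controlled trial to follow. That is true and limits the weight of the point. It does not remove it: knowing the average drift d would still not separate b from m, and the limitations in the Discussion list response bias, performance bias, social desirability and short duration, but not the missing control or culture's own influence.

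**The mismatch is partly one of words.** Section 3.6 in practice equates the app's effect with pre-post change, and on that reading the interaction tests what is stated. This stands in part, and it is why rewording is enough. But the language of 3.3 and 3.6 is causal, and the Abstract shows that a supportable wording was available.

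**The model is inferred.** The protocol says only that interaction terms will be used; it does not write culture by time. That is correct. An interaction of culture with app engagement is also conceivable and would have a different null. It would not rescue the claim, because engagement is self-selected and may itself depend on culture.

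**The rates rest on an assumed b.** This stands fully. They are the power of a slope test at chosen values of b, for a normal outcome, whereas the primary outcome is a 0 to 7 count of dichotomous items.

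**Conclusion.** The wording in 3.3 and 3.6 claims more than the design can deliver. Whatever the size of b, a single-arm pre-post interaction with culture estimates b + m and cannot be read as modification of the app's effect. That conclusion needs no numerical assumption.

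Its practical size is unknown. If b is 0 there is no distortion. Under the illustrative assumptions (n=50, SD of change 1), rejection with no true modification rises to about 11%, 28% and 53% at b of 0.1, 0.2 and 0.3.

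Three stronger readings are tempting, and the documents do not support them:

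- **That this pilot has a false-positive rate of 28% or 53%.** No document gives b, so these are conditional figures only.
- **That real modification would be hidden.** The algebra allows it when b and m have opposite signs. If a healthy culture slows decline, as the protocol's reasoning suggests, masking would require the app to work less well in healthy departments, and nothing in the protocol points that way.
- **That the later trial would be stratified or targeted on a false modifier.** The Discussion says the pilot will support that trial but does not mention using culture in its design.

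The point concerns a supplementary analysis in a small pilot, not the primary comparison.

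**What to change.** - In 3.3 and 3.6, replace the effect modification wording with the estimand the Abstract already implies: the association between Health Culture score and pre-post change during app use.
- Label the analysis exploratory and report the interaction as an estimate with a 95% CI.
- Add to the limitations that, without a concurrent control, this association cannot be attributed to the app, because culture may itself influence the course after the academy.
- Leave modification of the app's effect to the planned randomised trial, where a culture-by-arm term can address it.

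The cost is a few sentences and a weaker claim from a supplementary analysis. The model is the same and no new data are needed.

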### Ethics approval and data management

3.7

All protocols, questionnaires and procedures have been approved by the CHA Institutional Review Board and has received approval by the Compliance Assurance Program Office (CAPO) from the Department of Homeland Security. The IRB approved research will not begin without authorization from the CHA Office for Sponsored Research. All research activities will meet HIPAA Privacy and Security Rule and all members of the study team will comply to internal and external auditing by CHA Quality Assurance/Quality Improvement personnel. Signed consent forms and all data collection will be extracted and transferred to CHA password-protected internal servers and maintained confidentially. All electronic data will be restricted to authorized research personnel and will be password protected ensuring a low risk of breaching confidentiality. The study team will keep the key to the code in a password-protected computer and locked up for at least 7 years after study closure per OHRA’s Record Retention Policy. The research team will regularly review the data collected for the research project at least once a month to ensure data integrity throughout the duration of the research project.

### Dissemination

3.8

The findings of the current project will be disseminated through various approaches including but not limited to publications, media, conference and meeting presentations to national and international audiences, such as the New England College of Occupational & Environmental Medicine (NECOEM), the American College of Occupational & Environmental Medicine (ACOEM). In addition, the findings will be disseminated directly to the fire service including presentations at the U.S. National Fire Academy in collaboration with the National Fallen Firefighters Foundation (NFFF), the International Association of Fire Fighters (IAFF) and the International Association of Fire Chiefs (IAFC)/Safety Health and Survival Section (SHS).

## Discussion

4

This study protocol presents the proposed usability testing and piloting of a viable, user-friendly, healthy lifestyle app as a digital intervention tool for lifestyle behavior change among new, probationary firefighters in the US. Upon completion of the development of a full prototype overseen by the research team, the usability testing in the study target population will be followed by a satisfaction survey and focus groups, whereas the pilot study phase will observe the plausible changes in health behaviors to assess the feasibility of this novel mobile-app intervention.

Lifestyle-related diseases account for 2/3 of lifetime mortality among US firefighters, which can be largely attributed to major chronic disease risk factors, including unhealthy lifestyle behaviors such as tobacco, poor dietary quality, and physical inactivity (13). Notably, unhealthy dietary habits, overweight and obesity are prevalent among firefighters (3). Studies have shown that over 70% of US firefighters are either overweight or obese, exceeding the national average for adults in the US (61, 62) Additionally, hypertension, metabolic syndrome, dyslipidemia, and smokeless tobacco are also prevalent among US firefighters (63).

Recently, the occupational exposure as a firefighter was classified as carcinogenic to humans (Group 1) (64). While firefighters experience well-documented carcinogenic exposures (65, 66), there is substantial evidence that cancer risks are reduced by following healthy diets, engaging in regular physical activity, and avoiding obesity (67, 68). Similarly, other growing areas of concern regarding firefighters health include the negative consequences of repeated exposure to traumatic events that may lead to depression, post-traumatic stress, substance abuse, and suicide (3, 69, 70). There is significant evidence and data supporting that healthy behaviors reduce the risks of and can improve symptoms of depression and other mental health disorders. These healthy behaviors include adherence to a healthy diet (71), engaging in regular physical activity (72), avoiding excessive sedentary behavior (73), and a higher adherence to an overall HLS (11, 74). Thus, this study plays a role in occupational health care by overseeing the development of a digital tool for a comprehensive workplace health promotion and occupational health strategy with scientific vigor.

Despite existing evidence on the positive effects of good “safety” cultures in the fire service, studies are limited on health-promoting climates and firefighter health (56, 75). Evidence from our earlier case-control and national-level studies established the interaction of work duties with lifestyle among firefighters and underlying diseases associated with on-duty cardiac events (2, 5, 76). Yet, their risks can all be mitigated by better nutrition and other lifestyle measures (32). Our preliminary work has indicated the necessity and importance of a user-friendly HLS app intervention well suited to the new firefighters for better maintenance and improvement of HLS parameters (11).

To the best of our knowledge, this is the first HLS app that specifically addresses new firefighters’ health and well-being. Moreover, unlike most HLS apps who focus only on one or two lifestyle aspects, our app takes a more holistic approach and thoroughly covers four of the most essential HLS domains (nutrition, sleep, physical activity, resilience) (77–80). Thorough knowledge of the target population is instrumental to an app-based intervention’s success, therefore, *Surviving and Thriving* will be occupationally-tailored to new US firefighters. There is an important gap in the digital health movement to meet this particular workforce’s lifestyle needs, to not only survive but also thrive, in light of the demands of their career.

The creation of the app prototype was preceded by extensive literature reviews and even a qualitative study by our research team in order to investigate how to best accommodate the needs of our target population and how to best address potential facilitators and barriers to adherence to an HLS intervention (26). The educational content of the app was mainly derived from firefighter-specific resources and the graphics for the wireframes were designed to be firefighter-themed, where applicable. We also made sure that the daily workload associated with the app would be flexible enough to incur behavioral changes but not interfere with the work demands and busy lifestyle of professional firefighters. Most importantly, once pre-beta testing has been completed, the app will be evaluated by focus groups consisting of experienced firefighters at first and new firefighters after beta testing. Their feedback and ideas will then be used to optimize the app prototype before the pilot study phase and to ensure that the final version fits the end-users’ needs.

In order to counteract the high attrition and low long-term engagement rates traditionally associated with app-based interventions, we have employed multiple gamification strategies, a scoring system *(surviving* and *thriving* points*)* as well as the inclusion of a habit tracker and community missions (81). Other aspects targeting user engagement include goal setting, notifications that reinforce healthy behaviors, a leaderboard to compare users’ progress, levels and incremental challenges for the individual, team-based challenges, and allocation of points, coins, and badges for milestones) which have been shown to incentivize engagement, foster behavioral changes more effectively and make the use of an app more appealing (82, 83).

We recognize that our study and app prototype have some potential limitations. First, a potential response bias is dependent on quest completion rates and overall evaluations of individual performance and progress, which greatly rely on what the user reports and/or uploads, which may not be congruent with their actual behavior. Second, participants will be aware of their participation in a pilot study of a lifestyle behavior change tool and the fact that they are under observation, our pilot study will probably be susceptible to performance bias and social desirability. Third, it can be argued that the pilot phase, which spans 3 to 6 months, may be too short to gauge whether the app-based intervention will have a significant impact on the health outcomes of professional firefighters, whose careers are usually decades-long. Regarding the technical features of the app itself, at this stage there is no option to integrate data from other mobile apps that estimate a range of cardiometabolic and other health parameters that the user may be already using. Also, we recognize that there is limited personalization since all users will have the same set of tasks that are required to complete the avatar’s journey. Nonetheless, the order of their weekly quests/tasks will be arranged based on their baseline goal setting.

Ultimately, our goal is to develop and test the usability and feasibility of a viable, user-friendly and engaging HLS app that will help new firefighters maintain and improve their training-derived health/fitness levels more effectively, as compared to those before engaging with the HLS app. Firefighters that engage regularly with the app are expected to demonstrate measurable and plausible changes in the HLS parameters covered by the app (nutrition, sleep, physical activity, resilience) in the desired direction. The current research will support the implementation of this app as the primary intervention strategy in a multi-center controlled trial in the US fire service. The proposed future randomized clinical trial would collect laboratory tests to study the potential effect of this digital intervention on chronic disease risk factors in addition to habitual lifestyle behaviors. Ultimately, by sustaining the academy/training-derived health benefits into the probationary firefighter period, we expect firefighters will be more likely to maintain good health habits throughout their careers and thus increase their career longevity.
